Infant feeding styles and practices comprise the attitudes and behaviors that characterize caregivers’ approaches to maintaining or modifying children’s eating behaviors. We have limited information associating these feeding styles and practices with early childhood obesity [20, 21]. Responsive feeding, which involves properly interpreting and responding to the infant’s signals, is the recommended style [24]. Ethnic minority caregivers are more likely to exhibit non-responsive feeding styles (e.g., pressure feeding) relative to non-Latinx whites [6]. This difference in styles may be contributing to observed early-life obesity disparities [6]. Additionally, low levels of acculturation to the dominant American culture may be related to non-responsive styles and practices, [20, 25, 26] but results are inconsistent [27]. A better understanding of variation in feeding styles and practices can inform the identification of risk groups and the tailoring of interventions to them, as well as examining these relationships over time can help draw causal inferences and associations [28, 29].

Other caregivers (e.g., grandparents) are commonly involved in infant care and feeding, especially in ethnic minority families [30]. Non-parent caregivers’ infant feeding behaviors, especially those of relatives, have been associated with early childhood obesity [31–34]. However, there are only a handful of existing obesity interventions for young children that incorporate caregiver feeding styles and practices with nutrition advice, [35–37] and even fewer that account for the involvement of multiple caregivers in infant feeding [38]. They also start too late. Most begin with school-age children and target children 6 to 12 years of age [39]. The first 1000 days of life (i.e., conception through 24 months) constitute a critical period for optimal nutrition and development. Obesity interventions during this time period especially for low-income ethnic minority children, are still lacking [40–44]. Furthermore, few studies have engaged federally-funded programs, such as Early Head Start (EHS), which provides child development and family support services to infant and toddlers under the age of three in low-income families across the US [45].

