**Fig. 1 Fig1:**
[figure not shown]
Overview of the two study phases

Phase 1 is a mixed-method longitudinal study intended to characterize the caregiver context of infant feeding in low-income families. We hypothesize that non-responsive feeding styles and non-recommended feeding practices will predict steeper infant growth trajectories and obesity status. To test this hypothesis, we will create a cohort of 300 mother-infant pairs to assess variation in mothers’ feeding styles and practices and model the relation of feeding styles and practices to infant growth from 2 to 24 months and obesity at 24 months. We will also obtain feeding data and in-depth information from a subsample of 36 mothers and their identified other caregivers to provide contextual data on other caregivers’ involvement in infant feeding.

Phase 2 will utilize qualitative methods to develop content to be added to EHS’ existing nutrition program to create the enhanced intervention. Approximately 30 EHS-enrolled families and 30 EHS staff will participate in focus groups. This phase also involves a pilot cluster randomized controlled trial comparing the enhanced program to the existing program. Thirty EHS-enrolled mothers will participate in the trial.

Before we started the research, the University of California Riverside Institutional Review Board (IRB) approved all data collection procedures, study instruments, and informed consent documents. Additionally, the study team and EHS programs completed Memoranda of Understanding outlining roles and responsibilities in the partnership.

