#### Survey measures

Infant weight and length will be measured to produce the two dependent variables: infant growth and obesity. Weight will be measured to the nearest 0.1 kg using calibrated Seca scales. Recumbent length will be measured to the nearest 0.5 cm using standard length rods. We will use the Centers for Disease Control (CDC) and Prevention SAS Macros for the World Health Organization (WHO) growth charts to convert weight and length measures into z-scores. WHO reference standards of gender-specific weight-for-length z-scores at ages 2, 6, 12, and 24 months will be used to evaluate infant growth and obesity.

Infant growth will be calculated as the growth trajectory over the first 24 months of life, using growth curve models of weight-for-length z-scores. We will explore the trajectory with different starting points, using the infant’s birth weight-for-length (reported by mother and converted to z-score) as baseline z-scores.

Obesity at 24 months will be calculated by the child’s body mass index (BMI), the standard clinical measure of obesity in children 2 years and older. We will assess this measure as kilograms of weight per square meter of length, and derive age- and gender-specific BMI percentiles, weight-for-age and BMI-for-age z-scores according to US national standards.

Feeding styles will be measured by the Infant Feeding Style Questionnaire (IFSQ), [56] which has 63 items on infant feeding beliefs and behaviors and 20 additional behavioral items related to solid feeding for children over 6 months of age. The questionnaire captures five feeding styles (i.e., laissez-faire, pressuring, restrictive, responsive, and indulgent) previously validated in a low-income sample of parents of infants and toddlers. Feeding practices will be measured by the 28 items (33 at 12 months) from the Baby Basic Needs Questionnaire (BBNQ) [57] pertaining to feeding, such as whether the child is breastfed exclusively or in combination with formula, when breastfeeding ended (if applicable), whether the child is exclusively formula fed, whether the child is fed solid foods, when solid foods were introduced, and what solid foods and other beverages are fed.

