#### Statistical analysis

The study will use feeding styles and practices as two-way treatments, resulting in nested mixed models. In such models the fixed effects will be feeding styles (treated as a categorical variable with 5 levels for 5 feeding styles) and practices (treated as factors of composite scores for each feeding practice, such as exclusive breastfeeding and the introduction of solid food). The random effects will be caused by two types of correlations: those due to the infant characteristics, such as weight, and those due to clustering at multiple time points and within sites (infants’ families educated at the same sites). Accordingly, the R squared of the mixed model is expected to be at least 60%. The overall significance level α for a two-sided test is 0.05, and power 80%. Due to item similarities in a construct, the proposed significance level must be adjusted by the Bonferroni correction for multiple comparisons. In this study, the smallest adjusted significance level will be 0.0008 for each item in the construct of feeding beliefs and behaviors (0.05/63 items used in the construct of feeding practices). In addition, the hazard ratio across time points will be 1 for any reference level or group. Under these predefined conditions, the sample size will be 292, which was calculated in G*power 3.1.9.2.

Multiple imputation will be used if more than 5% of data is missing despite our efforts to prevent missing data. We will consider two types of effects: fixed and random. Thus, generalized linear mixed models will be ideal to analyze the data. Feeding styles and practices will be two categorical variables with fixed effects on the growth z score and obesity. Random effects will result from the nested grouping structure of infant families clustering in the same sites (like children in school classes) and the correlation between the variables, such as infant weight, collected from the same subjects across four time points. We will use generalized linear mixed models to examine if and how feeding styles and practices are associated with infant growth and obesity over time, and we will adjust these models for important covariates (e.g., mother’s pregnancy weight and age). Strongly associated items will be kept; all others will be excluded from further data analysis.

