Generalized linear mixed models will be built to assess how the different constructs and/or sub-groups of feeding styles and practices relate to infant growth and obesity, adjusting for important covariates. We will employ Poisson regression to predict obesity, measured as the count of infants who became obese. The effect sizes for infant growth will be presented as how their weights change the score mean and/or summations of different constructs and their subgroups over time. The effect sizes for obesity will be presented as hazard ratios to evaluate comparative contributions of the construct and/or different sub-groups to obesity over time. Results of these analyses will be: 1) clustering of feeding style and practice items into subconstructs and subgroups which can be identified as meaningful clusters; 2) variation in feeding styles and practices within the sample; and 3) as whole latent variables, how these constructs or their subscales comparatively affect infant growth and obesity. This information will inform the development of the enhanced intervention components.

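### The growth and obesity models are said to yield feeding-item clusters and variation in feeding, which they cannot estimate, and the item-exclusion rule would build constructs from outcome-selected items

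*Protocol article*

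**What the plan says.** The Survey measures section of the protocol article fixes the outcomes: "Infant weight and length will be measured to produce the two dependent variables: infant growth and obesity". It also says that the feeding style questionnaire captures five styles, previously validated in low-income parents of infants and toddlers.

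The Statistical analysis section gives feeding the role of predictor: "Feeding styles and practices will be two categorical variables with fixed effects on the growth z score and obesity". It continues: "We will use generalized linear mixed models to examine if and how feeding styles and practices are associated with infant growth and obesity over time", with adjustment for covariates. Items with a strong association are then retained, and all others leave the analysis. The section goes on: "Generalized linear mixed models will be built to assess how the different constructs and/or sub-groups of feeding styles and practices relate to infant growth and" the other outcome; and for obesity, "We will employ Poisson regression to predict obesity, measured as the count of infants who became obese".

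It then states what comes out: "Results of these analyses will be: 1) clustering of feeding style and practice items into subconstructs and subgroups", next the variation in feeding styles and practices in the sample, and last the comparative effects of the constructs, as latent variables, on growth and obesity. These results are to inform the enhanced intervention.

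Variation is also a stated purpose of the cohort. The Project overview says the study will "create a cohort of 300 mother-infant pairs to assess variation in" mothers' feeding styles and practices, and, as a separate task, model their relation to growth and obesity.

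**The concern.** Two of the three listed results are credited to models that do not estimate them. The models take constructs and subgroups of feeding as inputs, and the same text then lists subconstructs and subgroups among the outputs. The article describes no step that forms them.

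The only item-reduction rule described works on association, and it directly follows the sentence about association with growth and obesity. Anyone following the plan literally would screen items against the outcomes, group the survivors, call the groups feeding constructs, and report their effects on the same outcomes in the same infants. Such groups reflect shared association with the outcome, and the reported effects would be biased away from zero by the selection. Because the results are meant to shape the intervention content, both faults would carry into Phase 2.

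**Working it through.** No figure in the protocol is in dispute. The check is about which quantities the described models can give.

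**Step 1: the role of each variable.**
- Outcomes: infant growth and obesity (Survey measures).
- Feeding styles and practices: fixed effects (Statistical analysis).
- Ethnicity and acculturation: listed among the covariates (Survey measures).
- Phase 1 cohort analyses described with a feeding score as the outcome: none.
- Factor, cluster or other measurement method named for the survey items: none.

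**Step 2: each promised result against the models.** A regression describes the distribution of growth or obesity given feeding.
- Item clusters depend on the joint distribution of the items, on which the model conditions. Not estimated.
- Variation in feeding depends on the distribution of feeding across mothers, on which the model also conditions. Not estimated.
- Effects of constructs on growth and obesity: estimated, provided that the constructs have been formed beforehand.

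**Step 3: illustration of item exclusion (assumed values).** The protocol gives no threshold for a strong association. Its smallest adjusted level, 0.05/63 = 0.00079 (stated as 0.0008), was used. Assumed: 300 infants; 63 items in five true clusters, one of 13 items related to the outcome and four totalling 50 items unrelated; item = √0.4 × factor + √0.6 × noise; outcome = 0.3 × factor + site effect (12 sites, SD 0.3) + noise (SD 1); each item tested with site adjustment; 200 repetitions. This is a single-outcome simplification of the planned mixed model.
- Items kept on average: 5.6 of 63.
- Kept from the four unrelated clusters: about 0.01 of 50.
- Kept from the related cluster: about 5.6 − 0.01 = 5.59 of 13, or 43%.

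Four of the five true clusters vanish, and more than half of the fifth is lost. The rule selects items and does not recover how they group.

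**Step 4: the selection bias.** With 300 infants (298 degrees of freedom) and p < 0.00079, the critical t is about 3.39. A kept item must show an observed correlation of at least 3.39/√(3.39² + 298) = 3.39/17.6 = 0.19. In the illustration the true within-site correlation of a related item is 0.3 × √0.4/√(0.3² + 1) = 0.190/1.044 = 0.18. Every item that survives therefore shows a correlation above its true value.

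**Step 5: illustration of variation (assumed values).** Growth was regressed on a style score and a two-level group in 300 infants, with a true style effect of 0.3 and no group effect, over 500 repetitions. Only the difference in style between the groups was changed.

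| Group difference in style | Style coefficient | Group coefficient |
|---|---|---|
| 0 SD | 0.301 | 0.008 |
| 0.5 SD | 0.302 | 0.003 |
| 1.0 SD | 0.300 | 0.003 |

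The coefficients do not move. The growth model carries no information on who uses which style.

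**The case against.** The strongest reply is that this is loose wording in a condensed article. The article speaks of composite scores, constructs and latent variables, which suggests that items are grouped before modelling, and the five-style structure is already validated. The choice of factor or clustering method would normally sit in a fuller document. Plain variation in the sample needs only descriptive summaries of scores collected at 2, 6 and 12 months, and articles seldom spell those out.

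Much of this stands. An unnamed method would be no fault, and the variation result is easily supplied from the collected data. What does not fall away is that the article credits these results to the outcome models, and that it states an exclusion rule which runs against the first of them. No passage says that clusters will be read off regression coefficients, and the point does not need that.

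A reader might go further and infer that the study leaves a stated risk-group question unanswered. The documents do not support this. The Background says "A better understanding of variation in feeding styles and practices can inform the identification of risk groups and the tailoring of interventions to them", but that is rationale: neither the numbered aims nor the Phase 1 hypothesis asks for differences in feeding by ethnicity or acculturation. A reader might also want a power figure for such comparisons. The article gives no group sizes for the cohort and no target difference; its three sociocultural groups of 12 belong to the qualitative subsample of 36. No power claim is made here.

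**Conclusion.** The point holds for two of the three listed results as the text attributes them, and for the item-exclusion rule. The conclusion about the models follows from the stated roles of the variables and needs no numerical assumption. The view that exclusion works on the outcomes rests on reading the rule together with the sentence before it, which is its natural sense. The 5.6 of 63 items and the unchanged coefficients are illustrations under assumed values, not predictions for this cohort.

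The consequence is moderate. The data needed for all three results will be collected, and the third result can be obtained once scores exist. If the text is followed as written, however, the reported constructs would be outcome-selected sets of items with overstated effects, and variation, a stated purpose of the cohort, would have no analysis behind it. This should be corrected before the Phase 1 analysis starts.

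**What to change.** Rewrite the Statistical analysis section as three separate steps.

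1. **Measurement.** Form the style and practice scores from the feeding items alone, without outcome data. Start from the validated five-style structure, for example by confirmatory factor analysis. Remove the exclusion of items by their association with growth or obesity before this step.
2. **Variation.** Report the distribution of the style and practice scores by visit and by the ethnicity and acculturation variables already collected. Where groups are compared, make the feeding score the outcome. Descriptive tables are enough for variation in the sample as a whole.
3. **Association.** Enter the scores from step 1 in the growth and obesity models. This gives the third result.

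Then attribute each promised result to its own step. The choice among clustering or latent-class methods can stay with the study team, provided that it is made without the outcomes. The cost is revised wording and a little more analysis work, with no new data and no change to visits or sample size.

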#### Feeding data

Qualitative data on infant feeding and other caregiver involvement in infant feeding will be collected using the Baby Connect application (app) (https://www.baby-connect.com/home) and diary debriefing interviews. The Baby Connect app is the most comprehensive baby tracking application on mobile application stores. This app also has a web interface for parents who do not have an iPhone or Android smartphone to view and enter information. If participants do not have a smartphone or access to a computer with internet, we will provide them with a tablet with the app downloaded onto it.

Baby Connect is set up like a log to track solid food feeding, bottle feeding, and breastfeeding. Within each of these types, mothers can further select category options (e.g., Bottle feeding includes milk, water, formula, or juice). For each entry, the user can add text in a notes section. We will ask participants to describe other caregiver involvement in this section. The goal is to understand whether and how mothers translate their EHS nutrition education to practice in the context of other caregivers’ involvement in infant feeding. This app will provide data on: 1) whether mothers give directives to other caregivers, 2) if other caregivers follow those directives, and 3) how mothers respond to other caregivers’ infant feeding styles and practices.

Infant feeding data will focus on who fed the infant, how the infant was fed (e.g., breast or bottle fed, spoon fed), what food was fed (e.g., milk, thickeners, solid food), when/why the feeding ended, and interpersonal interactions during the feeding. This information will allow us to examine feeding styles and practices. Given that use of smartphones is prevalent among low-income populations, [61] we will use a popular app for data collection, in lieu of a paper-and-pencil diary, to reduce participant burden and increase compliance.

Previous research asked mothers to collect weekly diaries over 6 weeks and respond to six questionnaires, resulting in six data points and sufficient infant feeding data [62]. In consideration of participant retention, repeat assessment, and the daily demands of having an infant, we will collect six data points over 48 h, capturing at least two each of morning, afternoon, and evening feeding occasions. Data from the Baby Connect app will be downloaded to a .csv data format immediately following the end of the 48-h data collection period.

Within 3 days of completion of the feeding diary, trained interviewers will conduct 45–60 min feeding data de-briefings by phone with mothers. Interviewers will use a semi-structured interview guide to elicit in-depth data on feeding occasions identified via the feeding diary data related to conflict, such as differences in feeding styles and practices and communication approaches among caregivers (see Additional file 2 for interview guide).

#### Dyadic interviews

In-person dyadic interviews with mothers and other caregivers will be conducted after the completion of the feeding diary data collection when the infant is 6 months of age. Dyadic interviews, an interactive technique involving an interviewer and two participants, [63] will encourage the mother and other caregiver to interact with each other in response to open-ended questions about feeding events documented in the feeding diary. This technique allows the comments of one participant to evoke responses from the other participant, provides interviewers with an understanding of the relationship dynamic, and allows participants to co-construct their understanding of past events within their personal relationship [64]. A semi-structured interview guide will be used to elicit information on: 1) similarities and differences in infant feeding styles and practices between caregivers, 2) sources of conflict in infant feeding practices, and 3) ways to overcome conflict or communicate about disagreements (see Additional file 3 for interview guide). At the end of the dyadic interview, the trusted other caregivers will complete a brief survey to collect basic demographic information and responses to the IFSQ [56, 65].

#### Qualitative analysis of feeding data

The feeding data from the Baby Connect app and transcripts of the debriefing interviews will be analyzed using a deductive approach. A priori or predetermined codes from the interview guide (e.g., disagreement/conflict) and existing literature on common feeding styles and practices will be used as initial codes, as will key terms identified during the debriefing (e.g., communication approaches). We will use word-based techniques (e.g., Keywords-in-Context), which are rapid and efficient ways to locate specific examples of text for theme development. For feeding data, we will use this analytic technique to identify text related to caregiver roles, differences, and conflicts in infant feeding, which will inform probes for subsequent dyadic interviews.

The dyadic interviews will be transcribed and the textual data will be analyzed using an inductive approach. The analysis will begin during data collection to ensure theoretical saturation [66]. Text, mother and caregiver demographics, and IFSQ data will be imported into MAXQDA, [67] a qualitative, mixed-methods data analysis software program. Following MacQueen et al., [68] we will use open coding to read texts line by line to identify emergent themes and develop a team-based codebook. Once the codebook is established, in-vivo coding will be used to independently apply the codes to the same transcripts to assess inter-coder agreement, repeating this process until an acceptable inter-coder reliability of .80 is reached. Once an agreement is established, the analysts will apply the codes to the textual data. Axial coding, or constant comparison, will then be used to conduct a comparative analysis among mothers and trusted caregivers by their IFSQ scores.

